### Sample size calculation

We assume a small to medium effect (superiority of the two intervention groups over the control condition) on ED symptomatology. Repeated measures analysis of variance (ANOVA) will be conducted (time*group interaction, alpha = 5%). Assuming an effect of *f* = 0.15, a dropout rate of 20%, and correlations of 0.1 among repeated measures, 309 subjects need to be recruited (103 per group) to test the global hypothesis with 90% power. In case of significant findings for the main effect of study group, the proposed sample size will allow for post hoc pairwise group comparisons at a power above 80%.

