### Statistical analysis

Primary data analyses will be based on the intention-to-treat (ITT) population; i.e., all participants randomized to one of the three study conditions will be included in the primary outcome analysis. Missing data patterns will be explored. Multiple imputations will be applied to impute missing data.

Repeated measures ANOVA will be conducted (time*group interaction, alpha = 5%) to test the primary hypothesis, i.e., differences in efficacy between the interventions. For the primary outcome, only the baseline and the post assessment after 6 weeks will be considered. In case of statistically significant differences, post hoc pairwise group comparisons will be conducted (Bonferroni correction). Repeated measures ANOVA will also be conducted to determine the effect of the interventions on metric secondary outcomes. Post-intervention symptom courses will be analyzed applying mixed effects models. In order to investigate gender-specific efficacy, multifactor ANOVAs will be conducted. Fisher’s exact test will be applied to compare actual help-seeking between the groups.

For the health economic evaluation, data on the costs of interventions and efficacy will be used to determine the incremental cost-effectiveness ratio (ICER) of the interventions. The ICER will provide the additional costs in monetary terms of the respective programs to be spent for gaining an additional outcome unit. Cost-utility analyses will provide information on cost per quality-adjusted life years (QALYs) gained by the various interventions. Bootstrapping procedures will be applied to provide cost-effectiveness planes and acceptability curves.

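### The sample size section makes the pairwise comparisons conditional on the main effect of group, but the trial is sized and its primary hypothesis tested on the time-by-group interaction

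*Protocol article*

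**What the plan says.** Two sections of the protocol article bear on this.

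- **Sample size calculation.** The planned test is a repeated measures ANOVA with the time-by-group interaction at alpha 5%. The inputs are "Assuming an effect of *f* = 0.15", "a dropout rate of 20%, and correlations of 0.1 among repeated measures", giving 309 recruited (103 per group) "to test the global hypothesis with 90% power". The closing sentence begins "In case of significant findings for the main effect of study group" and says the sample size then allows "post hoc pairwise group comparisons at a power above 80" percent.
- **Statistical analysis.** "Repeated measures ANOVA will be conducted (time*group interaction, alpha = 5%) to test the primary hypothesis". The next sentence restricts the primary analysis to baseline and the 6-week assessment. The one after it says that, if differences are statistically significant, pairwise comparisons with Bonferroni correction follow. It does not say which effect has to be significant.

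The section on assessments places the baseline measurement before randomisation. The Primary outcome section defines the outcome as symptomatology at the end of the intervention.

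**The concern.** A repeated measures ANOVA with three groups and two time points yields separate F tests for group, for time and for their interaction. The interaction asks whether change from baseline to 6 weeks differs between arms, which is the treatment question. The group main effect asks whether the average of the baseline and 6-week scores differs between arms. Baseline precedes randomisation, so half of that average cannot carry a treatment effect. A difference that exists only at 6 weeks is halved, and chance baseline imbalance enters the comparison.

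The sample size section therefore powers one test and names another as the condition for the comparisons of each module with control. It is the only place in the article that names the gating effect at all. As a public pre-specification, the text lets someone who has seen the results cite either test as the planned gate.

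**Working it through.** **Inputs.** From the article: 3 groups, 2 time points in the primary analysis, f = 0.15, correlation r = 0.1, alpha = 0.05, 20% dropout, 309 recruited, 1:1:1 allocation. Assumptions made here: an effect at 6 weeks only and equal in both modules, equal variances at the two times, and correlations above 0.1 (used only to show the range).

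**Formulas.** Noncentral F with 2 and N − 3 degrees of freedom, and noncentrality
- interaction: N × f² × 2 / (1 − r)
- group main effect: N × f² × 2 / (1 + r)

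Under the assumed pattern, f = 0.15 corresponds to a 6-week difference from control of d = √(18 × 0.15²) = 0.64 SD. The average of the two scores then differs by d/2 = 0.32 SD with variance (1 + r)/2, which gives the second noncentrality. Both tests are thus evaluated under the same true effect.

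**Step 1: which test produced 309?**
- Interaction: 90% power needs N = 257 (noncentrality 257 × 0.045 / 0.9 = 12.85). Then 257 × 1.2 = 308.4, rounded up to 309, the stated figure.
- Main effect: 90% power needs N = 313 (noncentrality 313 × 0.045 / 1.1 = 12.80). Then 313 × 1.2 = 375.6, so 376.

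The stated size comes from the interaction and not from the main effect.

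**Step 2: power of each test as a gate.** Evaluable N = 309 × 0.8 = 247, and 247 × 0.045 = 11.115. Divide by (1 − r) or (1 + r):

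| r | Noncentrality, interaction | Power | Noncentrality, main effect | Power |
|---|---|---|---|---|
| 0.1 (stated) | 12.35 | 88.9% | 10.10 | 81.5% |
| 0.3 (assumed) | 15.88 | 95.3% | 8.55 | 74.2% |
| 0.5 (assumed) | 22.23 | 99.1% | 7.41 | 67.6% |
| 0.7 (assumed) | 37.05 | >99.9% | 6.54 | 61.8% |

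The gap widens as r rises, because correlation reduces the variance of a change score and increases the variance of an average.

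**Step 3: how often would the two tests disagree?** With equal variances at the two times, the sum and the difference of the scores are uncorrelated, so under normality the two decisions are practically independent. The chance of a significant interaction with a non-significant main effect is then
- r = 0.1: 0.889 × (1 − 0.815) = 0.16
- r = 0.5: 0.991 × (1 − 0.676) = 0.32

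Simulation agrees: 16–17% at r = 0.1 and 32% at r = 0.5.

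**The case against.** The strongest reply is that the article does not in fact gate on the main effect. The rule for conducting the comparisons belongs to the Statistical analysis section, where the condition follows directly on the interaction test and can hardly refer to anything else. The sentence in the sample size section is a statement about power; it does not forbid pairwise comparisons after a significant interaction. Step 1 supports this reading, since the main effect was plainly not the test used for planning. The phrase looks like a loose label for the overall group difference.

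Most of this stands, and it limits the point. A reader might infer that the pairwise comparisons are gated on the main effect instead of the interaction, so that a trial with a positive primary result would be barred from comparing modules with control. The documents do not support that: it requires a subordinate clause in a power statement to override the analysis section.

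A reader might also infer that a chance baseline difference could open the gate and produce false claims. That does not follow either. Each pairwise test must still pass Bonferroni, which controls the family-wise error with no gate at all. In a simulation of the global null with comparisons of change scores, the literal main-effect gate plus Bonferroni gave a false pairwise finding in about 0.2–0.3% of trials, against about 4–5% without a gate. A literal gate costs power; it does not inflate type I error.

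What the reply does not remove is the contradiction itself. The analysis section leaves its gating effect unnamed, and the one section that names it names a test that neither the primary hypothesis nor the sample size uses. This is stated wording, not detail left to a fuller plan.

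**Conclusion.** The article is internally inconsistent about the gate for its pairwise comparisons. The sample size section is wrong as written; the analysis section is right in context but does not name its effect.

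Under the literal reading only, with 247 evaluable and an effect at 6 weeks equal in both modules, the gate's power would be about 81% instead of 89% at the stated correlation, and about 68% instead of 99% at an assumed 0.5. At the stated correlation, about one trial in six would have a significant primary test and a closed gate. The figure of 247 applies the article's dropout rate and takes no account of the planned multiple imputation.

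The primary test, alpha and sample size are unaffected. Severity is minor to moderate.

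**What to change.** In Sample size calculation, replace the reference to the main effect of study group with the time-by-group interaction from baseline to 6 weeks. In Statistical analysis, name the same effect as the condition for the Bonferroni-corrected pairwise comparisons. Any separate statistical analysis plan should use the same wording.

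This changes one phrase in each section and needs no new data. The sample size stays at 309, since it was already derived from the interaction.

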Potential limitations and challenges of the present trial include the fact that uptake of and compliance with the interventions are unknown. Research on e-mental health in general has shown that rates of both intervention dropout and study dropout may be high in such trials, and that incomplete follow-up data often question the robustness of findings even when ITT analyses are conducted. Challenges with respect to recruitment and adherence have also been reported for ED-specific prevention efforts [55]. The inclusion of male participants in the trial also represents a challenge, as there is almost no research on ED prevention in male samples. However, given that EDs also affect boys and men, it is highly relevant to study interventions in male populations. In the present trial, the dissonance-based and CBT-based modules include specific contents for male participants. Finally, it is to note that the planned sample size will be too small to directly compare the efficacy of ProYouth-DISS and ProYouth-GROUP. Analyses on the relative efficacy will thus be explorative in nature.

In summary, we expect the present trial to make an important contribution to research in the ED field by informing us on the efficacy and cost-effectiveness of the newly developed prevention tools. In case of positive results, the nature of the interventions (e.g., the combination of automated and personalized components) and the availability of the technical infrastructure as part of the ProHEAD Consortium would allow for a broad dissemination and long-term sustainability of the interventions.

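### The claim of more than 80% power for pairwise comparisons does not hold unconditionally under the plan's own Bonferroni correction, and the Discussion contradicts it for ProYouth-DISS versus ProYouth-GROUP

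*Protocol article*

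**What the plan says.** In the protocol article, Sample size calculation, the assumed effect is "superiority of the two intervention groups over the control condition". The test is stated as "Repeated measures analysis of variance (ANOVA) will be conducted (time*group interaction, alpha = 5"%). The inputs are "Assuming an effect of *f* = 0.15, a dropout rate of 20%, and correlations of 0.1 among repeated measures", from which "309 subjects need to be recruited (103 per group) to test the global hypothesis with 90% power". The section then adds that, if the group effect is significant, "the proposed sample size will allow for post hoc pairwise group comparisons at a power above 80"%. It gives no alpha for these comparisons and does not restrict which pairs are meant.

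Under Statistical analysis, for the primary outcome "only the baseline and the post assessment after 6 weeks will be considered". The follow-up rule is "In case of statistically significant differences, post hoc pairwise group comparisons will be conducted (Bonferroni correction"). The number of comparisons to correct for is not given.

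The Discussion says that "the planned sample size will be too small to directly compare the efficacy of ProYouth-DISS and ProYouth-GROUP", and it calls analyses of relative efficacy explorative.

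**The concern.** The global test shows only that the three arms do not all change alike. Whether a given add-on improves on ProYouth alone, which is the stated objective, is answered by the pairwise comparisons. Their stated power is therefore the figure a reader uses to judge the chance of a clear answer for each add-on.

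That figure carries no alpha, while the analysis section corrects for multiplicity. If it was worked out at an unadjusted 5%, it describes a test that the trial will not perform. The three sections also disagree on the third pair. ProYouth-DISS versus ProYouth-GROUP falls within the general power claim and the general Bonferroni rule, yet the Discussion treats it as underpowered and exploratory. The Bonferroni divisor, two or three, is thus left open for the primary outcome.

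**Working it through.** **Inputs.** From Sample size calculation: f = 0.15, correlation ρ = 0.1, dropout 20%, 103 recruited per arm, alpha 5%. From Statistical analysis: m = 2 time points and Bonferroni. Completers: 309 × 0.8 = 247, or about 82 per arm. Three further assumptions are mine: both add-ons have the same benefit d over ProYouth, tests are two-sided, and the significant group finding that opens the pairwise step is the time-by-group interaction.

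**Step 1: reproduce the global power.** The noncentrality for the interaction is λ = N f² m/(1 − ρ) = N × 0.0225 × 2/0.9 = 0.05 N.
- N = 247: λ = 12.35, F with 2 and 244 df, power 88.9%.
- N = 257: λ = 12.85, power 90%.

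Since 257 × 1.2 ≈ 309, this is evidently the calculation behind the plan. An inflation factor of 1.2 leaves slightly fewer than 257 after 20% dropout, which costs about one point of global power.

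**Step 2: convert f to a pairwise difference.** With outcome SD 1, the change score has variance 2(1 − ρ) = 1.8. For the pattern (0, d, d), λ = N (2/9) d²/1.8. Setting this equal to 0.05 N gives d² = 0.05 × 1.8 × 9/2 = 0.405, so d = 0.636. That is 0.636/√1.8 = 0.474 SD of the change score.

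**Step 3: power of one comparison with ProYouth.** At 82 per arm the noncentrality is 0.636/√(1.8 × 2/82) = 3.04, with 243 pooled df. At 86 per arm (257/3) it is 3.11.

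| Alpha per comparison | 82 per arm | 86 per arm |
|---|---|---|
| 0.05, unadjusted | 85.7% | 87.3% |
| 0.025, Bonferroni over two | 78.2% | 80.3% |
| 0.0167, Bonferroni over three | 73.4% | 75.8% |

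**Step 4: allow for the global test as a gate** (simulation, 82 per arm).

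| Alpha per comparison | Given a significant global test | Global test and this comparison | Global test and both comparisons |
|---|---|---|---|
| 0.05 | 93.0% | 82.5% | 76% |
| 0.025 | 87.2% | 77.4% | 66% |
| 0.0167 | 82.6% | 73.3% | 60% |

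**Step 5: ProYouth-DISS versus ProYouth-GROUP.** Under equal benefit there is no difference to detect, so the rejection rate is just alpha. Under a graded pattern (0, d/2, d) with the same f, power for this pair at 0.0167 is 26%, the same as for the weaker add-on against ProYouth. The stronger add-on against ProYouth has 86%.

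**The case against.** The best defence is the sentence's opening condition. Read literally, it states power given a significant global test, and on that reading each comparison with ProYouth reaches 82.6% even with Bonferroni over three. This stands as a reading of the text, so the sentence cannot be called false on every reading. It does not give the chance that the planned trial demonstrates a given add-on's benefit, because it leaves out the trials stopped at the gate. That chance is 73% to 77%.

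Second, the planners appear to have sized for 86 per arm, where Bonferroni over two gives 80.3% (79.6% including the gate). The two-comparison shortfall is therefore borderline. Over three comparisons it remains clear at 76%. Counting all 103 per arm gives 84% at 0.0167, but only by setting aside the plan's own 20% dropout.

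Third, the assumed effect concerns superiority over control only, and the Discussion openly discloses the limit on the third pair. That makes the contradiction a matter of wording, but it still leaves the size of the Bonferroni family unsettled.

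Two stronger readings are tempting. A reader might infer that each effective add-on has more than a one-in-four chance of being missed. That needs the three-comparison divisor, which the article does not state; over two the miss rate is about 20% to 22%. A reader might also infer that the Bonferroni step is a mistake because the global gate already suffices. With three arms, the gate followed by unadjusted tests does control the family-wise error, but Bonferroni after a global test is valid, conventional and conservative. Choosing it is not an error.

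**Conclusion.** The point holds as a moderate one. Under the plan's own correction, unconditional power per comparison with ProYouth is about 73% over three comparisons and 78% over two, against a stated figure above 80%. The stated figure is reached unconditionally only at an unadjusted 5% (86%), or after correction only as power conditional on a significant global test. At 86 per arm the figures become 76% and 80%, so the three-comparison shortfall is firm and the two-comparison one is marginal. The contradiction over ProYouth-DISS versus ProYouth-GROUP rests on the text alone and needs no model.

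The percentages rest on equal benefit of the two add-ons, two-sided tests and loss of information from dropouts. The article gives no effect pattern beyond superiority of both arms.

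The primary global test is not affected. Its power is about 89%, no error rate is inflated, and the sample size was not derived from the pairwise claim. With the gate and Bonferroni over three, the chance of detecting at least one add-on is still about 87%.

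**What to change.** In Sample size calculation and Statistical analysis, name ProYouth-DISS versus ProYouth and ProYouth-GROUP versus ProYouth as the confirmatory follow-up. Describe ProYouth-DISS versus ProYouth-GROUP as exploratory, as the Discussion already does. State the alpha per comparison and restate the power to match: about 78% per comparison with Bonferroni over two, or 73% over three. Say whether the figure is conditional on the global test.

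As an option, decided and documented before the arms are compared, Bonferroni could be replaced by closed testing for three groups: after a significant interaction test, each pair is tested at an unadjusted 5%. Simulated family-wise error is about 5% under both the global and a partial null. Power including the gate is about 82% per comparison with ProYouth, and 76% for both.

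The cost is a wording change in the protocol and the analysis plan, with no extra participants or data. Restoring 80% with Bonferroni over three by recruitment instead would need about 94 analysable per arm (normal approximation). That is 94/0.8, or about 118 recruited per arm and 354 in total.

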### Statistical analysis

Primary data analyses will be based on the intention-to-treat (ITT) population; i.e., all participants randomized to one of the three study conditions will be included in the primary outcome analysis. Missing data patterns will be explored. Multiple imputations will be applied to impute missing data.

Repeated measures ANOVA will be conducted (time*group interaction, alpha = 5%) to test the primary hypothesis, i.e., differences in efficacy between the interventions. For the primary outcome, only the baseline and the post assessment after 6 weeks will be considered. In case of statistically significant differences, post hoc pairwise group comparisons will be conducted (Bonferroni correction). Repeated measures ANOVA will also be conducted to determine the effect of the interventions on metric secondary outcomes. Post-intervention symptom courses will be analyzed applying mixed effects models. In order to investigate gender-specific efficacy, multifactor ANOVAs will be conducted. Fisher’s exact test will be applied to compare actual help-seeking between the groups.

For the health economic evaluation, data on the costs of interventions and efficacy will be used to determine the incremental cost-effectiveness ratio (ICER) of the interventions. The ICER will provide the additional costs in monetary terms of the respective programs to be spent for gaining an additional outcome unit. Cost-utility analyses will provide information on cost per quality-adjusted life years (QALYs) gained by the various interventions. Bootstrapping procedures will be applied to provide cost-effectiveness planes and acceptability curves.

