#### ProYouth-DISS

A structured dissonance-based intervention will be provided as an add-on to ProYouth; i.e., participants will have access to an enhanced version of ProYouth for 6 weeks. The ProYouth-DISS intervention aims at reducing ED risk factors by inducing cognitive dissonance. This approach assumes that the thin ideal and thin-ideal internalization play a major role in the development of ED. Internalized thin ideals in combination with social comparison processes result in increased body dissatisfaction. High levels of body dissatisfaction can cause dieting, restrained eating, and other compensatory measures to reduce body weight. This can be considered one of the developmental pathways of ED. ProYouth-DISS aims at counteracting these processes by influencing the internalized thin ideal and other weight- and shape-related beliefs and attitudes. As part of the intervention, participants will be asked to actively criticize such dysfunctional attitudes and beliefs. The discrepancy between the participants’ own beliefs and attitudes and the position they are representing in this situation causes dissonance. Because of the human tendency to seek consistency between attitudes and behaviors, this dissonance is reduced by a change of beliefs and attitudes (e.g., thin-ideal internalization, body dissatisfaction). Female participants will learn to challenge the thin ideal. In addition, they will be asked to engage in exercises aimed at reducing body image concerns. Male participants have access to an adapted version of ProYouth-DISS that challenges the muscular body ideal [42]. Videos with peers guide participants through the program and motivate them to attend the sessions. Participants work through the materials individually and may interact with a counselor on demand. The module consists of six sessions. As part of the weekly ProYouth monitoring emails, participants will be reminded to complete the ProYouth-DISS sessions. In addition to the structured ProYouth-DISS module, participants are encouraged to use the standard ProYouth modules.

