#### ProYouth-GROUP

A clinician-guided CBT group intervention will be provided as an add-on to ProYouth. The preliminary efficacy of CBT interventions in terms of reduction of body image problems and ED symptoms has been confirmed in both face-to-face and online settings [27]. Based on this evidence, the ProYouth-GROUP intervention will use a CBT approach to address factors that contribute to the development and maintenance of body dissatisfaction, weight/shape concerns, and disordered eating. A specific focus will be on environmental risk factors such as stigmatization and the perceived pressure from peers and media to conform to social appearance ideals. This pressure is assumed to increase both the internalization of social appearance ideals and body comparison tendencies, which subsequently lead to an increase of body dissatisfaction, weight/shape concerns, and disordered eating. Therefore, the ProYouth-GROUP intervention will teach skills for understanding and counteracting such pressures from peers and media and convey ways how to normalize one’s own eating behavior. The group chats focus on topics such as media influences on body dissatisfaction, strategies to improve self-esteem and body image, and emotion regulation skills. In addition, participants are asked to engage in cognitive behavioral exercises following each session. The last session will highlight the importance of seeking help early, discuss barriers to help-seeking, and illustrate strategies on where and how to seek professional help. The intervention consists of six 90-min group chat sessions facilitated by a qualified psychologist. Separate groups will be established for female and male participants. Videos with peers guide participants through the program and motivate them to attend the chat sessions. They are also reminded to join the chat sessions as part of the weekly ProYouth monitoring emails. In addition to this structured module, participants are encouraged to use the standard ProYouth modules.

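### One arm is treated in chat groups, but the primary ANOVA and the sample size treat all participants as independent; any positive within-group correlation would push the test above its nominal 5%

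*Protocol article*

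**What the plan says.** Under Randomization and blinding, participants are allocated individually, 1:1:1, stratified by gender. The three arms then differ in how treatment is delivered:

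- **ProYouth-GROUP:** "The intervention consists of six 90-min group chat sessions facilitated by a qualified psychologist". Female and male participants are placed in separate groups. Group size and number of groups are not given.
- **ProYouth-DISS:** "Participants work through the materials individually and may interact with a counselor on demand".
- **ProYouth (control):** psychoeducation, a peer forum, optional chats and weekly monitoring. Participants in the other two arms are encouraged to use these modules as well.

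The Statistical analysis section names the primary test: "Repeated measures ANOVA will be conducted (time*group interaction, alpha = 5%) to test the primary hypothesis". It adds: "For the primary outcome, only the baseline and the post assessment after 6 weeks will be considered". Pairwise comparisons with Bonferroni correction follow only if the overall test is significant. Mixed effects models are named only for symptom courses after the intervention. The Sample size calculation uses the same test: "Assuming an effect of *f* = 0.15, a dropout rate of 20%, and correlations of 0.1 among repeated measures", with the result that "309 subjects need to be recruited (103 per group) to test the global hypothesis with 90% power". Neither section mentions chat groups, and clustering is not among the limitations in the Discussion.

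**The concern.** This is a partially nested design: individual randomization, with clusters formed after randomization in one arm only. Members of a chat group share a facilitator, fellow members and discussions about peer pressure and body image, and the primary outcome is measured as the sessions end. Some correlation of their outcomes is plausible.

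Repeated measures ANOVA has no place for that correlation. It computes the variance of the GROUP mean as if each participant contributed independent information. If the correlation is positive, the true variance is larger, so the omnibus test and both contrasts that involve GROUP reject too often under equal means. A contrast of DISS with ProYouth that uses only those two arms is not affected. The power promised for the GROUP contrast is also overstated. Conclusions about one of the two new modules, and the cost-effectiveness results built on them, would look more certain than they are.

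**Working it through.** **1. Reproduce the planned sample size.** Inputs from the Sample size calculation: f = 0.15, correlation 0.1, two time points, three groups, alpha 5%, power 90%, dropout 20%.

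Noncentrality for the time-by-group interaction: lambda = f² × N × 2 / (1 − 0.1), with 2 and N − 3 degrees of freedom. At N = 257, lambda = 0.0225 × 257 × 2 / 0.9 = 12.85 and power is 0.901; at N = 256 power is just under 0.90. Then 257 × 1.2 = 308.4, rounded up to 309. The stated figure is reproduced exactly, with independent participants and no design effect.

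**2. Set up the check.** With two time points, the interaction test equals a one-way ANOVA on change scores. Evaluable number per arm: 103 × 0.8 = 82. Only the GROUP arm is clustered, with design effect DE = 1 + (m − 1) × ICC for chat groups of m members.

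Assumptions, not in the documents: m from 5 to 10, ICC of the change score from 0 to 0.10, every GROUP participant in a group. For m = 8 and ICC = 0.05, DE = 1 + 7 × 0.05 = 1.35, so the true standard error of the GROUP mean is √1.35 = 1.16 times the one ANOVA uses. For m = 10 and ICC = 0.10, DE = 1.90 and the ratio is 1.38.

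**3. Type I error by simulation** (at least 100,000 trials per cell, equal means, pooled-variance ANOVA, nominal 5%):

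| ICC | 5 members | 8 members | 10 members |
|---|---|---|---|
| 0 | 5.0% | 5.0% | 5.0% |
| 0.01 | 5.2% | 5.4% | 5.5% |
| 0.02 | 5.4% | 5.5 to 5.8% | 6.0% |
| 0.05 | 6.0% | 6.9% | 7.5% |
| 0.10 | 7.2% | 8.9% | 10.0% |

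At ICC 0 group size is irrelevant. Repeat runs differ by about 0.2 points. With 103 per arm, which is closer to an intention-to-treat analysis with imputation, the figures are nearly the same.

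**4. The planned GROUP versus ProYouth contrast.** Requiring a significant omnibus test and then Bonferroni over three pairs (nominal 1.67%), the false-positive rate is about 1.6% without clustering, 2.6% at 8 members and ICC 0.05, and 4.6% at 10 members and ICC 0.10. These are two-sided. GROUP is falsely declared better than ProYouth in about 0.8%, 1.3% and 2.2% of trials respectively; false findings against it are as frequent.

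**5. Partial attendance.** Suppose half of the GROUP arm never joins a chat. If the attenders still fill groups of the stated size, omnibus error is about 5.9% (8 members, ICC 0.05) and 7.3% (10 members, ICC 0.10). If the groups simply shrink by half, it is about 5.3% and 6.0%.

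**6. Power of GROUP versus ProYouth.** Assume both modules are equally superior. The planned effect then gives f² on the change score of 0.0225 × 2 / 0.9 = 0.05, and a standardized difference of √0.05 × 3 / √2 = 0.474. The variance of the difference rises by (1 + DE) / 2 = 1.175 at 8 members and ICC 0.05. With 82 per arm and standard errors computed correctly, power falls from about 86% to 80% unadjusted, and from 73% to 65% with Bonferroni over three.

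**The case against.** The strongest objection is that the size is unknown. The article states no ICC, group size or number of groups. At ICC 0.01 or below the error is at most about 5.5%. If the module had no effect on anyone, sharing sessions would create no correlation; inflation needs group-specific effects that average to zero. The Discussion says uptake is unknown, and participants who never attend share nothing. All of this stands. A reader might infer that the primary test simply does exceed 5%, or that 10% is its expected error; the documents support neither.

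A reader might also infer a bias in favour of ProYouth-GROUP. That is not so. An understated variance leaves the estimate unbiased, and the excess rejections split evenly between the two directions.

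The overall test followed by Bonferroni correction gives some protection, and an unadjusted pairwise test at 5% is not what is planned, so only the gated figures are used for type I error above. Taking the correction over three pairs is itself an assumption, because the Discussion treats DISS versus GROUP as explorative. The article also does not say whether chat groups are closed or have rolling membership, and the forum and optional chats in all arms could produce some weaker dependence there too.

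Finally, it can be said that random effects and degrees of freedom belong in an analysis plan. That would answer an article that left the model open. This one names the primary model in two sections, and the sample size reproduces only under independence. An analyst who follows it would omit the chat group.

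**Conclusion.** The point holds in conditional form. The primary model and the sample size ignore the group delivery of one arm. For any positive within-group correlation, the standard error of the GROUP mean is too small, and the omnibus test and the GROUP contrasts exceed their nominal levels in both directions.

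The inflation is negligible at an ICC near 0.01, modest at 0.02 and material from 0.05 upward. These sizes rest on assumed group sizes of 5 to 10 and full attendance, and they shrink with non-attendance. The planned ANOVA can neither estimate nor absorb the correlation, so the uncertainty about its size is a reason to change the model.

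**What to change.** - Record the chat-group ID for each ProYouth-GROUP participant while the groups are running.
- For the primary outcome and the metric secondary outcomes, pre-specify a partially nested mixed model before results are seen: a random chat-group effect in the GROUP arm only, with participants in the other arms and those who join no group as singletons; arm-specific residual variance; Satterthwaite or Kenward-Roger degrees of freedom. If membership is rolling, adapt the group term, since one fixed group per person would not describe it.
- Restate the power of GROUP versus ProYouth over a stated range of ICC and group size, at the Bonferroni level that will be used. No additional enrolment is asked for.

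The cost is one stored variable and revised analysis wording. The downside is a slightly wider interval and a lower stated power for the GROUP contrast; if the correlation is near zero, little is lost.
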